### Aims and hypotheses

The study hypotheses and research questions are presented in Table 1. The primary aim is to examine the effectiveness of CIPE, delivered approximately 1 to 2 months after a trauma, as an indicated secondary prevention aimed at reducing PTSS and the incidence of PTSD. We will compare the effect of CIPE + treatment as usual (TAU) vs. TAU only, to examine whether CIPE has the potential to improve the ordinary psychosocial services provided by crisis teams. In such contexts, TAU (see “TAU” under the section “Interventions”) is considered to be an appropriate comparator with several benefits [26, 27]. TAU reflects the current real-world practice of the psychosocial crisis teams against which any added benefit of CIPE must be demonstrated, in order to evaluate if CIPE improves standard care and should be routinely implemented in Norwegian municipalities. The study was designed as an add-on trial (i.e., CIPE as an add-on) due to practical and ethical considerations.

**Table 1 Tab1:** Hypotheses and research questions in the EASE study

Hypotheses concerning the effectiveness and cost-effectiveness of CIPE	
H1	Participants receiving CIPE + TAU will have significantly less PTSS than participants receiving TAU at 6 weeks post T1, and at 6 and 12 months after the traumatic incident
H2	Significantly fewer participants receiving CIPE + TAU will fulfill the criteria for PTSD compared to participants receiving TAU, at 6 and 12 months post trauma
H3	Participants receiving CIPE + TAU will have significantly less symptoms of depression and insomnia than participants receiving TAU at 6 weeks post T1, and at 6 and 12 months after the traumatic incident
H4	Participants in the CIPE + TAU-condition will report significantly higher treatment satisfaction at post-treatment, compared to those in the TAU-condition
H5	Participants with traumatic loss receiving CIPE + TAU will have significantly less symptoms of prolonged grief than participants with traumatic loss receiving TAU 12 months after the loss
H6	Fewer participants in the CIPE + TAU-condition will be referred to second-tier specialty mental health services, and more will achieve improved quality of life within the first year after the traumatic incident, compared to participants in the TAU-condition
H7	The CIPE + TAU implementation is more cost-effective compared to TAU in the short run and may even dominate TAU in the long run (i.e., more effective and less costly)

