### Inclusion and exclusion criteria

Inclusion criteria are (a) persons that receive support from a municipal crisis team, after (b) exposure to a traumatic event (as defined by criteria A of the PTSD diagnosis in the DSM-5) [30] within 4 to 7 weeks before T1, (c) a total score of 10 or above on the PTSD Symptom Checklist (PCL-5) [31] at T1 (4–7 weeks post trauma, dependent on the time of inclusion), (d) age 16 or above, (e) written informed consent, and (f) writes and speaks Norwegian and/or English.

Exclusion criteria are (a) severe psychopathology (e.g., psychotic symptoms, or high suicide risk) or substance dependence syndrome in need of specialized health care (harmful use is not an exclusion criteria, as long as participants commit to not being under the influence when completing the intervention), (b) known or evident severe cognitive impairment, (c) ongoing traumatization, violence, or threats, (d) unstable dose of psychotropic medication 2 weeks prior to T1, and (e) concurrent therapy elsewhere at the time of T1.

The therapists in the current trial are crisis team health care workers in the included sites (most commonly nurses and social workers). All therapists received training in study procedures. Those delivering CIPE were required to undergo training in CIPE (see the “Therapist training and fidelity” section).

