**Fig. 2 Fig2:**
[figure not shown]
Schedule of enrollment, interventions, and assessments *Note*. CAPS-5: The Clinician-Administered PTSD Scale for DSM-5; CAPS-5 A-criteria: only the assessment of whether the A-criterion is fulfilled in the CAPS-5; CIPE: Condensed internet-delivered Prolonged Exposure; CSQ-8: Client Satisfaction Questionnaire; ISI: Insomnia Severity Index; MINI: The Mini-International Neuropsychiatric Interview version 6; PCL-5: PTSD Symptom Checklist for DSM-5; PHQ-9: Patient Health Questionnaire-9; PTE: Potentially Traumatic Experiences; ReQoL: Recovering Quality of Life; SLESQ: The Stressful Life Events Screening Questionnaire; TAU: Treatment as Usual, TGI-SR+: The Traumatic grief inventory-self report plus.*Administered only to participants who receive support from the crisis team due to traumatic loss.**Administered in the CIPE+TAU-arm only

At enrollment, the crisis teams and the research group decide whether inclusion criterion B is met, using the Clinician-Administered PTSD Scale for DSM-5 (CAPS-5) [32] A-criterion assessment. If eligible by self-report measures at T1, the participants are assessed with the Mini-International Neuropsychiatric Interview (MINI) [33] version 6 and the CAPS-5 by trained graduate clinical psychology students. The interviews are completed by telephone. ERL (licensed clinical psychologist and PhD candidate) monitors the process. The estimated flow of participants throughout the study phases is visualized in Fig. 1.

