### Randomization

Eligible participants are randomized 1:1 in random block sizes of 4, 6, or 8 to either CIPE + TAU or TAU only, using the Sealed Envelope software [36] at T1. To mitigate the risk of contamination across treatment conditions, participants from the same household are cluster-randomized. The randomization is stratified on the level of municipal crisis teams to ensure an even distribution of cases in each treatment condition across municipalities. An independent, blinded senior researcher is responsible for all randomization procedures. The allocation is revealed to the study coordinator only after the T1 assessment and decision of inclusion are completed.

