#### Secondary outcome measures

The Clinician-Administered PTSD Scale for DSM-5 (CAPS-5) [32] is a 30-item structured interview, developed to assess current and lifetime PTSD diagnosis, as well as past-week PTSD symptoms. The instrument measures the 20 DSM-5 PTSD symptoms, in addition to the onset and duration of symptoms, related subjective distress, and functional impairment (social, occupational), amongst other aspects of the disorder. Standardized questions and probes are provided. A Norwegian version of the CAPS-5 [45] is administered at T1 and T3–4. CAPS-5 has excellent psychometric properties [32, 46]. The recall period is 1 week at T1, and 1 month at T3 and T4.

The Mini-International Neuropsychiatric Interview (MINI) [33] version 6 is a brief, structured clinician-administered interview designed to assess 17 DSM/ICD diagnoses. Standardized questions and probes are provided. A Norwegian translation of the MINI [47] is administered at T1. The interview has good psychometric properties [33, 48, 49].

A Norwegian version [50] of the Stressful Life Events Screening Questionnaire (SLESQ) [51] is administered at T1 to measure self-reported lifetime exposure to traumatic events. The respondents are asked to report exposure to 15 categories of traumatic events (“yes” or “no”), age at the time of the incident, as well as frequency and duration of the events. Other aspects of the incidents are reported, as well. The Norwegian version of the SLESQ incorporates two extra items compared to the original 13-item version: “Have you ever been directly affected by a natural disaster?” and “Has anyone outside your family, such as fellow pupils or colleagues, repeatedly ridiculed you, put you down, ignored you, or told you were no good?”. The SLESQ has satisfactory validity and reliability [51, 52].

The Patient Health Questionnaire (PHQ-9) [53] is a 9-item self-report measure of depressive symptom severity. The recall period is 2 weeks. Response is given on a 4-point Likert-type scale (0: not at all, 1: several days, 2: more than half the days, and 3: nearly every day), resulting in a total score ranging from 0 to 27. Higher scores indicate higher symptom severity. The instrument is sensitive for both clinical and sub-clinical levels of depressive symptoms and has good psychometric properties [53, 54]. We administer a validated Norwegian version of the PHQ-9 [55].

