The Insomnia Severity Index (ISI) [56] is a 7-item questionnaire that measures insomnia symptoms during the past 2 weeks. The instrument utilizes a 5-point Likert-type scale ranging from 0 to 4, yielding a total score of 0–28. Higher scores indicate more insomnia symptoms. The ISI has good psychometric properties [56–58]. A Norwegian version of the ISI is applied.

The Client Satisfaction Questionnaire (CSQ-8) [59] is an eight-item measure of participants’ service satisfaction. Response is given on a scale ranging from one to four, with a resulting total score ranging from 8 to 32. Higher scores suggest higher service satisfaction. A validated Norwegian version of the CSQ-8 is applied [60]. The CSQ-8 is adapted to the context of psychosocial crisis teams in the current trial (e.g., “treatment” adapted to “support”, “therapy” adapted to “support”).

The Traumatic Grief Inventory-Self Report Plus (TGI-SR+) [61] is a 22-item self-report questionnaire measuring symptoms of DSM-5 persistent complex bereavement disorder (PCBD) and ICD-11 Prolonged grief disorder (PGD) in participants who experienced traumatic bereavement. Response is given on a 5-point Likert-type scale ranging from 1 (“never”) to 5 (“always”). The total score ranges from 22 to 110, with higher scores indicating more severe symptoms. The instrument, including the Norwegian version applied here, has good psychometric properties [62, 63]. The instrument is administered at a 12-month follow-up and applies a recall period of the past month.

The EuroQol 5‑Dimension 5‑Level Questionnaire (EQ-5D-5L) [64] assesses self-reported health-related quality of life. It has five items: self-care, mobility, pain/discomfort, usual activities, and anxiety/depression, each measured on a 5-level severity scale (no, slight, moderate, severe, or unable/extreme problems). The instrument defines 3125 possible health states, valued by a representative sample of the general Norwegian population using the hybrid valuation method—composite time-trade-off and discrete choice experiment [65]. The utility scores are anchored on a − 0.453—1 scale, with 1 indicating “full-health,” 0 equivalent to “being dead,” and values below 0 are worse than being dead. The EQ-5D-5L data are used to generate quality-adjusted life year (QALY) used for cost-utility analysis (CUA). The instrument has excellent psychometric properties [66].

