### Statistical analyses

H1–3 are tested with linear mixed effects models. The linear mixed effects model includes fixed effects for treatment group (intervention vs. control) and time (post-intervention, 6 and 12 months). In a hierarchical setup, a second step includes a treatment × time interaction. Random effects include random intercepts for participants to account for individual differences. The mixed effects models are applied using the R package nlme [70]. H4–6 are examined using independent t-tests. The quality-of-life change (change in QALY) of participants in CIPE vs. TAU (H6) is analyzed using the mixed effects model. Estimation is conducted using restricted maximum likelihood, with all available observations included, yielding unbiased estimates under the assumptions of missing at random or missing completely at random. For the t-tests, missing data are handled using multiple imputation.

Hypothesis 7 involves a comprehensive economic evaluation comparing the cost-effectiveness of CIPE relative to TAU in terms of both costs and consequences/effectiveness [71]. Costs are assessed using the ingredients approach, which involves three steps: first, identifying each resource required for the intervention; then, measuring these resources; and finally, valuing them. The effectiveness of the intervention is measured by QALY—a composite measure combining both quantity of life (mortality) and quality of life (morbidity) into a single metric [72]. For each arm, mean costs and mean QALYs are estimated across all participants to calculate the incremental cost (ΔC) and incremental effect (ΔQALY). The incremental cost-effectiveness ratio (ICER) or incremental cost per incremental QALY (ΔC/ΔQALY) is then calculated for decision-making. To accept the intervention, ICER should be less than the willingness-to-pay or cost-effectiveness threshold. Since there is no official threshold in Norway, we apply a threshold recommended by the Norwegian Directorate of Health (NOK 500 000 at 2005 prices), adjusted to current price levels [73].

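### H5 is fixed as an unadjusted t-test on 12-month grief scores although T1 PCL-5 is available for every randomised participant; the test is valid but gives up some precision

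*Protocol article*

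**What the plan says.** Under Aims and hypotheses (Table 1), H5 predicts that participants with traumatic loss in the CIPE + TAU arm will have "significantly less symptoms of prolonged grief than participants with traumatic loss receiving TAU 12 months after the loss". The outcome is the TGI-SR+. Under Secondary outcome measures, "The instrument is administered at a 12-month follow-up and applies a recall period of the past month", and the note to Fig. 2 adds: "Administered only to participants who receive support from the crisis team due to traumatic loss". The text describes no T1 grief score.

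The test is named under Statistical analyses: "H4–6 are examined using independent t-tests". No covariate is mentioned. The same section says that missing data for the t-tests are handled by multiple imputation, without naming the imputation variables.

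The inclusion criteria require "a total score of 10 or above on the PTSD Symptom Checklist (PCL-5) [31] at T1", and the Data collection section places T1 before randomisation. CAPS-5 is also taken then: "A Norwegian version of the CAPS-5 [45] is administered at T1 and T3–4". On allocation, "The randomization is stratified on the level of municipal crisis teams", in a 1:1 ratio, and participants from the same household are randomised as a cluster.

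**The concern.** An independent t-test admits no covariate, so naming it excludes use of T1 severity in the H5 comparison. This is a stated method, not a detail left open.

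Two things are lost. First, whatever part of the variation in 12-month grief T1 symptom severity predicts stays in the error term. Second, if the bereaved arms happen to differ in T1 severity, the estimate is not corrected for it. Stratification is by crisis team only, so neither bereavement nor T1 severity is balanced by design, and a non-trivial imbalance is plausible in a small subgroup.

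Precision is scarce here. H5 concerns a subgroup of unstated size, at the visit by which the protocol expects 40% overall attrition, and has no power statement of its own.

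**Working it through.** **Inputs from the protocol article.** Test: independent t-test (Statistical analyses). Allocation 1:1 (Randomization). Expected 12-month completers: 360 × (1 − 0.40) = 216, which reproduces the stated figure (Power and sample size calculations). The protocol gives no sample size, effect size or power for H5, so there is no H5 figure to reproduce.

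**Assumed inputs.** (a) The bereaved share of completers is not stated. 50% is used for illustration: 216 × 0.50 / 2 = 54 per arm. 25% gives 27 per arm. (b) The correlation r between T1 PCL-5 and 12-month TGI-SR+ is not stated. The range 0.2 to 0.6 is shown. Low values belong in it because PCL-5 measures a different construct, about 10 months earlier. (c) Two-sided alpha 0.05, 80% power, independent observations, completers only (no imputation).

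**Step 1: detectable difference with the t-test.** 54 per arm gives d = 0.544; 27 per arm gives d = 0.777.

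**Step 2: effect of adjustment.** Adjusting for one baseline covariate multiplies the residual variance by (1 − r²). The detectable d is multiplied by √(1 − r²), and the equivalent sample-size factor is 1/(1 − r²).

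| r | 1 − r² | Equivalent extra participants | Detectable d, 54 per arm | Detectable d, 27 per arm |
|---|---|---|---|---|
| 0 (t-test) | 1.00 | – | 0.54 | 0.78 |
| 0.2 | 0.96 | 4% | 0.544 × 0.980 = 0.53 | 0.76 |
| 0.3 | 0.91 | 10% | 0.544 × 0.954 = 0.52 | 0.74 |
| 0.5 | 0.75 | 33% | 0.544 × 0.866 = 0.47 | 0.67 |
| 0.6 | 0.64 | 56% | 0.544 × 0.800 = 0.44 | 0.62 |

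**Step 3: the same gain as power.** With 54 per arm and a true d of 0.5, power is 73.1% unadjusted and 74.8%, 77.0%, 84.4% and 89.6% at r = 0.2, 0.3, 0.5 and 0.6. The noncentral t is used, with one degree of freedom spent on the covariate.

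**Step 4: chance imbalance.** The SD of the difference in mean T1 score between arms, in baseline SD units, is √(2/n per arm): √(2/54) = 0.19. An imbalance at the edge of the 95% range is 1.96 × 0.192 = 0.38 SD. It moves the unadjusted grief difference by r × 0.38: about 0.11 SD at r = 0.3 and 0.19 SD at r = 0.5. For scale only, the protocol's expected effect for its primary hypothesis is d = 0.3.

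**The case against.** The strongest reply is that nothing here is an error. Randomisation follows T1, so the unadjusted comparison is unbiased over randomisation and its standard error already allows for chance imbalance. Ignoring the crisis-team strata normally makes a t-test conservative. All of this stands. A reader might infer that the H5 estimate is biased, or that an imbalance between the bereaved arms is to be expected. The documents support neither. Not stratifying on bereavement adds no bias, and the expected attrition is a missing-data matter rather than a source of chance imbalance.

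The second reply is that the benefit may be small. This also stands. TGI-SR+ has no baseline of its own, nothing in the documents shows how well T1 PCL-5 predicts grief at 12 months, and the PCL-5 entry threshold restricts the range of the covariate, which tends to lower the correlation. Quoting only correlations of 0.4 and above would overstate the gain.

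Third, the planned test is run after multiple imputation, so completer figures are not exactly the planned analysis. That is a fair limit on the numbers, but it does not remove the point: T1 scores in an imputation model inform the missing outcomes and do not adjust the comparison among observed cases.

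Finally, covariate lists often belong in a SAP, and one that is not shown might contain an adjusted sensitivity analysis. But the article does not leave the method open. It names a test that takes no covariate.

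**Conclusion.** The point holds as a minor, optional improvement. H5 is fixed as a valid but inefficient test, although a pre-randomisation severity score exists for every participant in the comparison. The size runs from slight (4% to 10% more participants, r = 0.2 to 0.3) to useful (33% to 56%, r = 0.5 to 0.6). With an assumed 54 bereaved completers per arm, the detectable difference at 80% power falls from 0.54 to between 0.53 and 0.44.

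These figures rest on an assumed correlation and an assumed bereaved share. They ignore imputation and household clustering. Relatives bereaved by the same death may share a household, so the detectable differences could be somewhat larger than shown with either method. H5 is a secondary subgroup hypothesis, and the primary result does not depend on it.

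**What to change.** Replace the H5 t-test with a pre-specified linear model of 12-month TGI-SR+ on arm and T1 PCL-5, with T1 PCL-5 as the single, fixed covariate. Account for crisis team, the stratification factor, and for household randomisation through household-clustered standard errors or a household random effect. With 21 crisis teams and an assumed 108 bereaved completers there are about 5 per team (108/21), so state in advance how crisis team enters and what is done if a random intercept cannot be estimated. Put T1 PCL-5 in the multiple imputation model as well.

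Do not leave the covariate list open. In particular, the text does not confirm that PHQ-9 is given at T1, and the schedule figure is not available here.

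The cost is wording only: no new data, visits or participants. The Trial status section reports that recruitment is ongoing, so the change can be fixed before any 12-month comparison is made.

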### Data collection

Figure 2 presents the trials’ enrollment, intervention, and measurement schedule. Participants enrolled within 3 weeks after the incident are assessed with self-report measures at the time of enrollment (T0). All participants are subsequently assessed before randomization (T1), post-treatment (T2), and at 6-month (T3) and 12-month (T4) follow-ups. The main outcome will be measured at post-treatment (T2). Self-report data from participants are collected using an electronic survey solution offered by BASS at the Karolinska Institute, Stockholm. The same system is used to obtain written informed consent and to deliver CIPE. Links to questionnaires are sent to responders using SMS and email. Data from the therapists are collected using Nettskjema and Services of sensitive data (TSD) at the University of Oslo (see “data management and storing”). The research coordinator monitors the data collection process and sends reminders to reduce attrition rates.

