The recovering quality of life (ReQoL) is an 11-item outcome measure assessing psychopathology-specific quality of life in mental health contexts [67]. For each item, response is given on a 5-point scale (never to most of the time or always). The study also uses the ReQoL utility index (ReQoL-UI), which is a recovery-focused generic preference-based measure derived from ReQoL. ReQoL-UI constitutes six mental health items (activity; belonging; choice, control, and autonomy; hope; self-perception; and well-being) and a physical health item, each with five severity levels. The ReQoL-UI defines 78,125 different health states valued by a representative member of the UK public using a conventional time-trade-off method [68]. The ReQoL-UI is also used to generate QALYs for CUA in mental health interventions. The ReQoL-UI values range between − 0.195 (for the worst health state) and 1 (for the full-health state), with zero indicating a health state equivalent to being dead.

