This economic evaluation is conducted in two ways: trial- and model-based approaches. In the former, we compare trial-specific intervention costs and effects. Following recommendations by NICE [74], we perform a cost-utility analysis combining intervention-related and wider healthcare costs with changes in QALYs. In the latter, we develop a decision analytic model to simulate the long-term (lifetime) cost-effectiveness of CIPE. The model extrapolates beyond the trial period to estimate the potential lifetime costs and QALY outcomes under different assumptions. In both approaches, model parameter uncertainty is assessed using both probabilistic and deterministic sensitivity analyses.

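### H7 describes ΔQALY as a difference in arm mean QALYs with no stated adjustment for T1 utility, so chance imbalance carries partly into the ICER and precision is lost

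*Protocol article*

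**What the plan says.** All references are to the protocol article.

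- **H7 estimator (Statistical analyses).** "For each arm, mean costs and mean QALYs are estimated across all participants to calculate the incremental cost" and the incremental effect ΔQALY. The "incremental cost per incremental QALY (ΔC/ΔQALY) is then calculated for decision-making", and the ratio is compared with a threshold of NOK 500 000 per QALY in 2005 prices, uprated to current prices.
- **Trial-based evaluation (same section).** The cost-utility analysis is described as "combining intervention-related and wider healthcare costs with changes in QALYs". The last term is not defined. The sensitivity analyses named there deal with parameter uncertainty.
- **H6, a separate hypothesis (same section).** "The quality-of-life change (change in QALY) of participants in CIPE vs. TAU (H6) is analyzed using the mixed effects model". The mixed model set out in that section has "fixed effects for treatment group (intervention vs. control) and time (post-intervention, 6 and 12 months", a second-step interaction of the two, and a random intercept. It lists no T1 value.
- **Source of the QALYs (Secondary outcome measures).** "The EQ-5D-5L data are used to generate quality-adjusted life year (QALY) used for cost-utility analysis (CUA"), and "The ReQoL-UI is also used to generate QALYs for CUA in mental health interventions".
- **Visits (Data collection).** "All participants are subsequently assessed before randomization (T1), post-treatment (T2), and at 6-month (T3) and 12-month (T4) follow-ups".
- **Allocation (Randomization).** The ratio is 1:1, stratified by crisis team only. Nothing in the design balances T1 utility between the arms.

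**The concern.** Utilities from one person at successive visits are correlated, and T1 utility is normally also the first point of a QALY computed over the trial period. If one arm happens to start with a higher mean utility, a plain difference in mean QALYs credits it with part of that head start. ΔQALY is the denominator of the ICER, so the quantity used for the decision inherits the shift. The variation that T1 utility could explain also stays in the standard error, which makes the uncertainty around ΔQALY wider than the trial's own data would require.

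**Working it through.** The plan states no figure for the precision of ΔQALY, so there is none to reproduce. The check asks what a difference in arm means would do, compared with a regression on arm and T1 utility.

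**Inputs from the protocol article**
- Visits: T1 at 4–7 weeks after trauma, T2 six weeks after T1, then 6 and 12 months. Midpoints used: 5.5, 11.5, 26 and 52 weeks.
- Twelve-month completers (Power and sample size calculations): 360 × (1 − 0.40) = 216, or 108 per arm at 1:1.

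**Assumptions, not in the documents**
- Utility SD σ of 0.15 to 0.25, the same at every visit.
- The same correlation ρ between any two visits, 0.3 to 0.7.
- QALY as the trapezoid area under the utility curve from T1 to 12 months.
- No allowance for household clustering.

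**Step 1: trapezoid weights in years.** Intervals are 6, 14.5 and 26 weeks.
- T1: 3/52 = 0.058
- T2: 10.25/52 = 0.197
- 6 months: 20.25/52 = 0.389
- 12 months: 13/52 = 0.250
- Sum: 46.5/52 = 0.894. Sum of squares: 0.256.

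**Step 2: pass-through.** The change in expected QALY per unit of T1 utility is b = w₁ + ρ(w₂ + w₃ + w₄) = 0.058 + 0.8365ρ.

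**Step 3: variance explained.** In units of σ², Var(QALY) = (1 − ρ) × 0.256 + ρ × 0.894². The squared correlation with T1 utility is r² = b²/Var(QALY), which is the proportional variance cut from adjustment.

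| ρ | b | Var(QALY)/σ² | r² (variance cut) | SE reduction, 1 − √(1 − r²) |
|---|---|---|---|---|
| 0.3 | 0.31 | 0.419 | 23% | 12% |
| 0.5 | 0.48 | 0.528 | 43% | 24% |
| 0.7 | 0.64 | 0.637 | 65% | 41% |

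**Step 4: central case (108 per arm, σ = 0.20, ρ = 0.5).**
- SE of the T1 difference between arms: 0.20 × √(2/108) = 0.0272.
- Shift in ΔQALY from a one-SE imbalance: 0.476 × 0.0272 = 0.013.
- SE of ΔQALY, unadjusted: 0.20 × √(2 × 0.528/108) = 0.0198.
- SE of ΔQALY, adjusted: 0.0198 × √(1 − 0.429) = 0.0149.

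**Step 5: range of the shift at 108 per arm.**
- Low end (σ = 0.15, ρ = 0.3): 0.309 × 0.15 × √(2/108) = 0.0063.
- High end (σ = 0.25, ρ = 0.7): 0.643 × 0.25 × √(2/108) = 0.0219.
- Valued at NOK 500 000 per QALY (2005 prices), the central shift is 0.013 × 500 000 = NOK 6 500 per person. The ends are about NOK 3 150 and NOK 10 950.

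**Step 6: would a change from T1 do the same job?** Subtracting T1 utility × 0.894 years from each QALY makes the T1 weight 0.058 − 0.894 = −0.8365. The weights then sum to zero and Var = (1 − ρ) × 0.953σ². At 108 per arm and σ = 0.20:

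| ρ | SE unadjusted | SE change from T1 | SE regression-adjusted |
|---|---|---|---|
| 0.3 | 0.0176 | 0.0222 | 0.0155 |
| 0.5 | 0.0198 | 0.0188 | 0.0149 |
| 0.7 | 0.0217 | 0.0146 | 0.0128 |

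A change score is less precise than regression at each of these correlations. At 0.3 it is worse than making no adjustment.

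**Step 7: sensitivity to T1 timing.** With T1 at 4 weeks the last three weights are 0.212, 0.404 and 0.250, so b at ρ = 0.5 is 0.058 + 0.5 × 0.866 = 0.49. With T1 at 7 weeks they are 0.183, 0.375 and 0.250, so b is 0.058 + 0.5 × 0.808 = 0.46. The choice matters little.

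**The case against.** The strongest reply is that the article never calls the means raw or unadjusted. It says they are estimated, which model-based means would also satisfy. An article condenses a fuller plan, and a health-economic plan that is not shown may name covariates. The undefined wording about changes in QALYs might also mean change from T1, which would already use the T1 utility.

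Part of this stands. A reader might infer that the sponsor has decided on a crude comparison, and the text does not establish that. What remains is that the only calculation described for H7 is a difference of arm means, with no baseline term in it or near it. The mixed model on QALY change is assigned to H6 and lists no T1 covariate. If a fuller plan does adjust, the article's description needs correcting. If change from T1 is meant, Step 6 shows that it is not an equal substitute.

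A second reply also stands: collection of the utilities at T1 is not confirmed. The Data collection section has all participants assessed at T1 but names no instrument, and the measure descriptions give no time points for EQ-5D-5L or ReQoL. The schedule figure is not available here, and its note lists ReQoL but not EQ-5D-5L. The H6 wording about change in QALY implies a T1 value without proving it.

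A third reply is that the sizes are almost wholly assumed. That is correct, and they are given as ranges for that reason.

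**Conclusion.** The point holds as a matter of conditional imbalance and lost efficiency. As described, H7 does not use T1 utility. Under the stated assumptions, a one-standard-error chance imbalance moves ΔQALY by about 0.006 to 0.022 at 108 per arm, and adjustment would cut its variance by about 23% to 65%. The direction of the precision gain is the same at every correlation examined, but its size depends on SDs and correlations that the plan does not give.

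Two stronger readings are not supported.
- **That the imbalance passes in full into the ICER, or biases it.** Pass-through is partial, about 0.3 to 0.6 per unit, and randomization leaves no bias in expectation.
- **That an ordinary imbalance would carry the ICER across the threshold.** The documents give no incremental cost or expected ΔQALY, so no crossing can be shown.

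**What to change.** In Statistical analyses, replace the arm-means sentence for the effect side with wording such as: ΔQALY is the treatment coefficient from a regression of each participant's QALY on arm and T1 utility, using EQ-5D-5L utility for the EQ-5D-5L QALY and ReQoL-UI utility for the ReQoL-UI QALY; the trial-based ICER and its uncertainty analysis use this adjusted increment; unadjusted arm means are shown descriptively. In the same edit, define what changes in QALYs means and confirm that both utility instruments are given at T1.

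The cost is a few sentences and one covariate, with no new data if the utilities are already collected at T1. One addition is needed: a stated way to impute missing T1 utilities, because the plan specifies multiple imputation only for the t-tests. The decision model can be left alone here, since its structure is not described. Trial status estimates that recruitment ends in September 2026 and the project in December 2027. Settling the choice before results are seen would rule out a later choice between adjusted and unadjusted ICERs.
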